**Methods/design:**

We will recruit 162 paediatric oncology patients and their families to a single centre randomised controlled trial. Patients from regional and remote areas, classified by Accessibility/Remoteness Index of Australia (ARIA+) greater than 0.2, will be randomised to a videotelephone support intervention or a usual support control group. Metropolitan families (ARIA+ ≤ 0.2) will be recruited as an additional usual support control group. Families allocated to the videotelephone support intervention will have access to usual support plus education, communication, counselling and monitoring with specialist multidisciplinary team members via a videotelephone service for a 12-week period following first discharge home. Families in the usual support control group will receive standard care i.e., specialist multidisciplinary team members provide support either face-to-face during inpatient stays, outpatient clinic visits or home visits, or via telephone for families who live far away from the hospital. The primary outcome measure is parental health related quality of life as measured using the Medical Outcome Survey (MOS) Short Form SF-12 measured at baseline, 4 weeks, 8 weeks and 12 weeks. The secondary outcome measures are: parental informational and emotional support; parental perceived stress, parent reported patient quality of life and parent reported sibling quality of life, parental satisfaction with care, cost of providing improved support, health care utilisation and financial burden for families.

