### Measurement

The SF-12v2 will be used to measure the primary outcome measure, parental health related quality of life. The SF-12 is a valid and reliable measure [30,31] used in a number of countries including Australia. More recently the SF-12 has been used in caregiver quality of life research [32].

Secondary outcome measures for parents will be: the informational/emotional subscale of the Medical Outcomes Study (MOS) Social Support Survey (a valid and reliable instrument for quantifying social support [33]), the 4-item Perceived Stress Scale (PSS) [34] and the FAMCARE scale (a valid and reliable instrument designed specifically to assess satisfaction with advanced cancer care [35]). For patients and siblings the Pediatric Quality of Life Inventory (Peds QL) parent proxy will be used (a valid and reliable measure of quality of life in children applicable to healthy populations and those with chronic disease [36]). In addition the Health Utilities Index Mark 2 (HUI2) will be completed by parents and used to assess patient quality-adjusted life years (QALYs).

Data collection will be undertaken via: user logs, chart audits, service database reviews, telephone and in-person interviews. Data collection with parents will begin at baseline (after consent has been obtained). The interviewer will be blinded to group allocation. Interviews will be used to obtain: demographics, baseline SF-12 scores, baseline informational and emotional support scores, baseline patient and sibling quality of life scores, and baseline satisfaction scores.

To reduce participant burden the completion of the various interview components will be staggered (Table 1). The initial interview will be the longest.

**Table 1 T1:** Interview schedule.

Component	Week												
	0	1	2	3	4	5	6	7	8	9	10	11	12
Demographics													
SF-12v2													
Informational/emotional support													
Perceived stress													
Patient quality of life													
Sibling quality of life													
HUI2													
Satisfaction													
Health care utilisation													
Family costs													

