### Data analysis

#### Sample size calculations

A total of 162 participants will be included in the study (based on data provided by the tertiary paediatric oncology referral centre this is feasible for a 24-month trial with a 20% refusal/attrition rate), 108 in the control group – 54 metropolitan and 54 regional and remote, and 54 in the regional and remote intervention group. Sample size calculations are given for the two main comparisons and economic analyses:

1. Regional and remote intervention group vs regional and remote usual support control group

- To test whether the provision of videotelephones to families in regional and remote areas can improve the health related quality of life of parents caring for a child with cancer over usual care, a unpaired t-test of the mean difference will be used [38]. This will be based on the SF-12 at week 12.

- As no paediatric caregiver research using the SF-12v2 has been undertaken in Australia to date, published evidenced available on paediatric parental caregiver burden in the US [39] and US norms [31] (Table 2) have been used as a guide for the sample size calculation. A clinically important difference would be to improve mean mental health related quality of life of parents (SF-12 Mental Component Summary [MCS]) in the intervention group by 7.5 points. This figure is further supported by calculation of SF-12v2 standard error of measurement [SEM], calculated as the standard deviation of an instrument multiplied by the square root of one minus its reliability coefficient [40]. With an SD of 10 and reliability coefficient of 0.86 [31], the MCS-12 has an SEM of 3.74. Evidence by Wywrich [41] supports the use of one SEM as an approximation of the *minimal *clinically important difference [MCID] of a psychometric instrument. Using this approximation, an improvement in MCS-12 of 7.5 represents two times the MCID, which is a large clinically important difference.

**Table 2 T2:** Published evidence available on the SF-12 health-related quality of life instrument.

Context	n	Details	Mean	SD
The impact of paediatric tracheotomy on parental caregiver burden and health status (US)[39]	154	PCS-12 MCS-12	50.5 35.8	11.3 11.4
US Norms[31]	7069	General US population		
		PCS-12	49.63	9.91
		MCS-12	49.37	9.75
		Depression		
		PCS-12	45.55	11.71
		MCS-12	37.40	10.76

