- Based on an improvement in MCS-12 mean in the intervention group of 7.5, and using SF-12v2 norm-based scoring methods (US general population SF-12v2 mean of 50 and SD of 10 [31]), at a power of 90% and a two-sided significance level of 1%, a sample size of 108 will be required, i.e. 54 in the intervention group and 54 in the control group.

2. Regional and remote intervention group vs metropolitan usual support control group

- To test whether the provision of videotelephones to families in regional and remote areas can improve the mental health related quality of life of parents to a level equivalent to that of metropolitan families receiving usual support, a test of equivalence will be used (according to the equivalence method described by Matthews [42]).

- With a two-sided significance level of 1%, sample size of 54, a mean difference between groups of zero and an equivalence bound of plus/minus 7.5, the study has a power of 87.2% for finding a genuine equivalence.

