#### Statistical analysis

Data analysis will be on an intention-to-treat basis and consist of univariate analysis between randomised groups on the primary and secondary outcomes. A more in-depth analysis will use longitudinal methods to account for correlations within families and to examine changes over time.

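### For the randomised comparison, the named unadjusted t-test on week-12 SF-12 is valid but gives up precision that the collected baseline score would supply without new data

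*Protocol article*

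**What the plan says.** All references are to the protocol article.

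- **Sample size calculations, comparison 1** (intervention versus usual support, both regional and remote) names the test: "a unpaired t-test of the mean difference will be used". It adds: "This will be based on the SF-12 at week 12".
- **Statistical analysis** says the intention-to-treat analysis will "consist of univariate analysis between randomised groups on the primary and secondary outcomes". It then plans a more in-depth longitudinal analysis of change over time. It names no baseline covariate and no week-12 contrast for that model.
- **Abstract, Methods/design** says that SF-12 is "measured at baseline, 4 weeks, 8 weeks and 12 weeks".
- **Measurement** confirms the baseline collection: "Interviews will be used to obtain: demographics, baseline SF-12 scores". The same sentence lists baseline values for informational and emotional support, patient and sibling quality of life, and satisfaction.
- **Sample size calculations** derives 108 families (54 per arm) for 90% power at a two-sided 1% level: "Based on an improvement in MCS-12 mean in the intervention group of 7.5", with a "US general population SF-12v2 mean of 50 and SD of 10".

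**The concern.** A parent's baseline score on a scale is usually a good predictor of the same parent's score 12 weeks later. The test tied to the sample size uses the week-12 score alone, so variation between parents that baseline could explain stays in the error term. Adjustment for baseline multiplies the error variance by 1 − r², where r is the within-arm correlation between baseline and week 12.

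What is at stake is the width of the confidence interval for the main randomised contrast, and the trial's tolerance of a larger SD or of missing interviews. The article names its method, so this is more than a detail left to an unseen analysis plan.

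**Working it through.** **Inputs from the article.** Difference δ = 7.5 points on MCS-12; SD = 10; two-sided α = 0.01; power 90%; n = 54 per arm. Table 2 also gives an MCS-12 SD of 11.4 in US parents of children with a tracheotomy. A combined refusal/attrition rate of 20% appears in the feasibility remark.

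**Assumed inputs.** r is not in the article, so 0.3, 0.5 and 0.7 are used. The value of 43 per arm assumes that the whole 20% is lost after enrolment: 54 × 0.8 = 43.2.

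**Step 1: reproduce the stated sample size.**

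n per arm = 2 (z₀.₉₉₅ + z₀.₉₀)² SD² / δ² = 2 × (2.576 + 1.282)² × 100 / 56.25 ≈ 52.9, so 53 per arm or 106 in total, against a stated 108.

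The standard error at 54 per arm is 10 × √(2/54) = 1.92, and the noncentrality is 7.5 / 1.92 ≈ 3.90. Power is 90.7% by the normal approximation and 89.6% by the exact noncentral t with 106 degrees of freedom. The stated figure reproduces.

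**Step 2: adjust for baseline.**

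Residual SD = SD × √(1 − r²). Power is then taken from the noncentral t with 2n − 3 degrees of freedom.

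| r | 1 − r² | Residual SD (SD 10) | Variance removed |
|---|---|---|---|
| 0.3 | 0.91 | 9.54 | 9% |
| 0.5 | 0.75 | 8.66 | 25% |
| 0.7 | 0.51 | 7.14 | 49% |

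**Step 3: power for a difference of 7.5 at the 1% level.**

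| Scenario | t-test | r = 0.3 | r = 0.5 | r = 0.7 | r needed for 90% |
|---|---|---|---|---|---|
| 54 per arm, SD 10 (as planned) | 89.6% | 92.6% | 96.8% | 99.7% | about 0.11 |
| 54 per arm, SD 11.4 | 78.5% | 82.9% | 90.5% | 98.4% | about 0.49 |
| 43 per arm, SD 10 | 79.8% | 84.0% | 91.3% | 98.6% | about 0.47 |
| 43 per arm, SD 11.4 | 66.1% | 71.2% | 80.9% | 94.6% | about 0.63 |

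Only the first row uses the article's planning values. The other three are what-if cases.

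**Step 4: the same gain as sample size.** By the normal approximation at SD 10, 90% power needs 53 per arm unadjusted, and 49, 40 or 27 per arm at r = 0.3, 0.5 or 0.7.

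**The case against.** The strongest reply is that nothing here is wrong. A t-test between randomised arms is unbiased, holds its type I error and matches the sample size calculation. Covariates are often left to the analysis plan. The first part stands in full. The second stands only in part, because the article does name an unadjusted test for this comparison.

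A reader might also infer several stronger things that the article does not support:

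- **That the trial is underpowered and adjustment would repair it.** On the article's own inputs there is no shortfall beyond rounding (89.6% against 90%). The lower figures need an SD of 11.4 or a loss to 43 per arm. The 20% combines refusal, which precedes enrolment, with attrition, and the article does not say that 54 will fall by that amount. Nor is repair assured: at r = 0.3 neither case alone returns to 90%.
- **That chance baseline imbalance biases the result.** Such imbalance is already part of the sampling error that the t-test allows for. Reducing its effect is the same precision gain, not a second benefit.
- **That the t-test breaks the intention-to-treat commitment by dropping families without a week-12 interview.** The article states no rule for missing week-12 scores, so no conflict can be shown.
- **That the week-4 and week-8 scores go unused.** The planned longitudinal analysis would use them. What remains open is which analysis is primary, and whether baseline enters as a covariate.

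Two limits apply to the remedy. Measurement places baseline after consent, and Randomization has envelopes opened as families enrol; the order of the two is not stated. A baseline taken after an unblinded family knows its allocation could itself be affected by allocation. In comparison 2 the metropolitan group is not randomised, so adjustment there would also change what is estimated.

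**Conclusion.** The point holds as an efficiency weakness in comparison 1. The named analysis is valid and the sample size of 108 is right for its inputs, but precision available from data already being collected is left out of the main test. At the planned size and SD, power rises from 89.6% to between 92.6% and 99.7% for r between 0.3 and 0.7. If the SD or the number analysed were less favourable, adjustment could make up the loss, given r of about 0.47 to 0.49 or more for either change alone and about 0.63 or more for both together.

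These figures rest on the assumed r, a linear relation between baseline and week-12 scores with the same slope in both arms, and baseline measured before allocation is known.

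**What to change.** For comparison 1, state that the primary analysis is the week-12 difference in mean MCS-12 between the randomised arms, adjusted for baseline MCS-12. Use either ANCOVA or the planned longitudinal model with baseline as a covariate and a week-12 contrast, and say which one. State that the baseline interview is completed before the allocation envelope is opened.

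Keep the unpaired t-test as a supportive analysis, and let the sample size of 54 per arm stand as a conservative calculation. Apply the same adjustment, in the randomised comparison only, to each secondary scale that has a baseline value.

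The cost is a sentence or two in the analysis section and, if it is not already the practice, a fixed order of baseline interview and allocation. No new data are needed.

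### The stated 90% and 87.2% powers rest on the general-population SD of 10 alone and do not hold at the larger MCS-12 SDs that the protocol's own Table 2 gives for distressed groups

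*Protocol article*

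**What the plan says.** All of this stands in the protocol article under *Sample size calculations*.

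- **Sources.** The section notes that no Australian paediatric caregiver work with the SF-12v2 exists and that "published evidenced available on paediatric parental caregiver burden in the US [39] and US norms [31] (Table 2) have been used as a guide".
- **Table 2, MCS-12 rows.** Paediatric tracheotomy caregivers: n = 154, mean 35.8, SD 11.4. US general population: mean 49.37, SD 9.75. US depression norm: mean 37.40, SD 10.76.
- **Comparison 1** (regional and remote intervention against regional and remote control). At week 12, "a unpaired t-test of the mean difference will be used". The size is "Based on an improvement in MCS-12 mean in the intervention group of 7.5", with norm-based scoring and a "US general population SF-12v2 mean of 50 and SD of 10". The result is that "at a power of 90% and a two-sided significance level of 1%, a sample size of 108 will be required", that is, "54 in the intervention group and 54 in the control group".
- **Comparison 2** (regional and remote intervention against metropolitan control). Equivalence power is given as 87.2% for 54 per group, a true difference of zero, bounds of ±7.5 and a two-sided 1% level. No SD is named.

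**The concern.** The caregiver study is named as a guide to the sample size, yet its SD does not enter the calculation, and power is shown at one SD only. Norm-based scoring sets the SD near 10 in the reference population. It does not make the SD 10 in another group, and in Table 2 both distressed groups exceed 10. The Background describes families caring for a sick child at home as having high levels of depression and anxiety, so the general-population row is not the obvious match for the trial's parents.

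Both comparisons are at stake. Equivalence with metropolitan families is the trial's second hypothesis, and its power falls fastest as the SD rises. If the SD is nearer the caregiver value, a null result or a failure to show equivalence would be read against more power than the trial had.

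**Working it through.** **Inputs.** n = 54 per group; difference or margin 7.5; level 1%; SD 10 (text), 10.76 and 11.4 (Table 2).

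**Formulas.** SE = SD × √(2/54), with 106 degrees of freedom.
- Superiority: noncentral-t power with noncentrality 7.5/SE and two-sided 1% critical value 2.623.
- Equivalence: two one-sided t-tests, true difference 0, each at 1% (critical value 2.362). Power is the probability that the observed difference lies within ±(7.5 − 2.362 × estimated SE), averaged over the distribution of the sample SD.

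**Step 1: reproduce the plan at SD 10.** SE = 10 × √(2/54) = 1.925 and noncentrality = 7.5/1.925 = 3.90.
- Superiority power is 89.6% by noncentral t and 90.7% by the normal approximation. The size needed for 90% is 55 per group by t and 53 by the normal approximation, so 54 is sound.
- Equivalence power is 87.2%, the plan's figure. At 0.5% per side it would be 79.2%; at SD 9.75 it would be 89.5% (1% per side) or 82.6% (0.5% per side). Of the SDs in this section, only 10 with 1% per one-sided test returns 87.2%. The SD behind comparison 2 is therefore inferred to be 10.

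**Step 2: change only the SD.**

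| SD | Source | SE | 7.5/SE | Superiority power | Equivalence power | n per group for 90% superiority |
|---|---|---|---|---|---|---|
| 10 | norm-based | 1.925 | 3.90 | 89.6% | 87.2% | 55 |
| 10.76 | depression norm | 2.071 | 3.62 | 83.9% | 78.8% | 63 |
| 11.4 | caregivers | 2.194 | 3.42 | 78.5% | 70.6% | 71 |

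The normal approximation at SD 11.4 gives 80.0% and 72.5%, so the choice of method matters little.

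**Step 3: baseline adjustment of comparison 1 at SD 11.4.** Adjusting for baseline MCS-12 reduces the SD to 11.4 × √(1 − r²), where r is the correlation between baseline and week 12. The documents give no r, so a range is assumed.

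| r (assumed) | Adjusted SD | Superiority power, 54 per group |
|---|---|---|
| 0.2 | 11.17 | 80.5% |
| 0.3 | 10.87 | 82.9% |
| 0.4 | 10.45 | 86.3% |
| 0.5 | 9.87 | 90.5% |

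**The case against.** **The arithmetic is right and the input is disclosed.** This stands. A reader might infer a miscalculation, but the plan's figures reproduce at its stated SD. The text calls the caregiver study and the norms together a guide and does not say that the caregiver SD was adopted. SD 10 is also slightly above the general-population value of 9.75. The criticism is of a planning assumption tested at one value only.

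**The caregiver SD is not the SD of cancer parents.** This also stands. A reader might infer that the trial's real power is 78.5% and 70.6%. The documents do not support that: 11.4 comes from one US study of a different condition, and no SD is given for parents of children with cancer. The value supports a range. Even the middle value, 10.76, misses both stated powers.

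**The 7.5 points depend on the same SD.** This stands in part. The section supports 7.5 as twice the standard error of measurement, 2 × 10 × √(1 − 0.86) = 7.48. At SD 11.4 that becomes 2 × 11.4 × √0.14 = 8.53 points, for which power at 54 per group is 89.5%. But 7.5 is also stated as an absolute clinically important difference, and it is the fixed equivalence bound, so the concern is not removed.

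**Attrition makes matters worse.** A reader might take a further 20% off the 54. The text does not support this. The 20% covers refusal and attrition together and is attached to recruitment feasibility. With about 100 new patients a year (Background), 100 × 2 × 0.8 = 160, close to the planned 162, so the allowance may already be netted out.

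**Longitudinal analysis is already planned.** It may recover some power, but the stated sizing is for an unadjusted week-12 t-test.

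**Conclusion.** The concern holds as a point about the planning SD and not as an arithmetic error. The stated powers are correct at SD 10 and do not hold at the SDs of the distressed groups that the protocol itself tabulates. Across SD 10 to 11.4, power runs from 89.6% to 78.5% for superiority and from 87.2% to 70.6% for equivalence. This assumes 54 analysed per group, a fixed 7.5 points, a true difference of zero for equivalence, and 1% per one-sided equivalence test. These are sensitivity figures, since the SD in cancer parents is unknown.

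The matter is worth correcting but does not threaten the trial. The tests stay valid, and even at the largest SD superiority power is 78.5% at a strict 1% level.

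**What to change.** 1. Restate both powers over SD 10 to 11.4: about 90% to 78.5% for superiority and about 87% to 70.6% for equivalence. Name the SD and the per-side level used for equivalence.
2. Make the primary randomised week-12 comparison an ANCOVA on MCS-12 with baseline MCS-12 as covariate, in place of the unpaired t-test. Baseline SF-12 is already collected (*Measurement*), so no extra families or visits are needed. The gain depends on the baseline correlation, which should be given as an assumed range: about 80% to 90% power at SD 11.4 for r from 0.2 to 0.5.
3. Do not count on baseline adjustment to restore power for the metropolitan equivalence comparison. That group is not randomised, so adjustment there changes the question asked as well as the precision.

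The cost is a less favourable power statement and a changed primary-analysis sentence.

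### The plan does not say whether 162 families is the number recruited or the number analysed at week 12; if recruited, any later loss takes power below the stated 90% and 87.2%

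*Protocol article*

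**What the plan says.** All of this is in the protocol article.

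- **Abstract, Methods/design:** "We will recruit 162 paediatric oncology patients and their families to a single centre randomised controlled trial".
- **Sample size calculations, opening paragraph:** 162 participants are to be included, 54 in each of the three groups. On the 20%, it says only that "this is feasible for a 24-month trial with a 20% refusal/attrition rate".
- **Sample size calculations, comparison 1** (regional and remote intervention against regional and remote usual support): an unpaired t-test, of which the plan says "This will be based on the SF-12 at week 12". The inputs are "Based on an improvement in MCS-12 mean in the intervention group of 7.5" and "US general population SF-12v2 mean of 50 and SD of 10", with 90% power and a two-sided 1% level. The result is that "a sample size of 108 will be required, i.e. 54 in the intervention group and 54 in the control group".
- **Sample size calculations, comparison 2** (intervention against metropolitan usual support): an equivalence test with 54 per group, a true difference of zero and a bound of ±7.5. The conclusion is that "the study has a power of 87.2% for finding a genuine equivalence".
- **Background:** the unit sees around 100 newly diagnosed patients a year, and around 60% of families live in regional and remote areas.

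**The concern.** The figure of 54 per arm comes from a formula for the number of scores compared at week 12. The abstract applies the same figure to recruitment. The plan names attrition as something it expects, but that expectation enters neither power calculation. It appears only where the plan argues that 162 is achievable in 24 months.

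Read literally, then, the number recruited equals the number that must be analysed, and every family lost between recruitment and week 12 comes off the 54. The stakes are the two headline power statements. The equivalence comparison carries Hypothesis 2 and loses power faster than the superiority comparison. A reader who relies on 87.2% could take a failure to show equivalence as evidence about the intervention when it partly reflects missing interviews.

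**Working it through.** **Inputs.** From Sample size calculations: difference and equivalence bound 7.5, SD 10, two-sided 1%, 90% power, 54 per arm, 20% refusal/attrition. From Background: about 100 new patients a year, about 60% regional and remote.

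**Step 1: reproduce the stated figures.**

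*Superiority, normal approximation:* n per arm = 2 × (2.576 + 1.282)² × (10/7.5)² = 52.9, so 53. The plan's 54 is consistent with this. At 54 per arm the standard error is 10 × √(2/54) = 1.92 and the standardised difference is 7.5/1.92 = 3.90. Power is 90.7% by the normal approximation and 89.6% by the noncentral t. The t-test needs 55 per arm to pass 90%, so 54 leaves no slack.

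*Equivalence:* two one-sided t-tests at true difference zero have power 1 − 2 × P(T ≤ t_crit), where T is noncentral t with 106 degrees of freedom and noncentrality 3.90. At 1% per one-sided test this gives 87.2%, which matches the plan. At 0.5% per one-sided test it gives 79.2%, which does not.

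The two comparisons therefore use different conventions. Below, superiority is at two-sided 1% (0.5% per side) and equivalence is at 1% per one-sided test. Neither calculation contains an attrition term.

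**Step 2: if 162 is the number recruited.** The same formulas (t-based) at smaller analysed numbers:

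| Analysed per arm | Loss after recruitment | Superiority | Equivalence |
|---|---|---|---|
| 54 | none | 89.6% | 87.2% |
| 51 | about 5% | 87.5% | 84.1% |
| 49 | about 10% | 85.8% | 81.8% |
| 43 | about 20% | 79.8% | 72.7% |

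The article does not split refusal from attrition, so the 5% and 10% rows are assumptions. The last row treats all of the 20% as loss after recruitment and none as refusal, so it is an upper limit on the loss.

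**Step 3: if 162 is already net of the 20%.** About 100 a year for 24 months is 200 patients, and 200 × 0.8 = 160, close to 162. (Conversely, 162/0.8 = 202.5.) On this reading the 54 per arm are analysed families and Step 1 stands.

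The regional and remote share then has to be checked separately: 200 × 0.6 × 0.8 = 96 families, or 48 in each randomised arm, against the 108 and 54 required. With 48 per arm, superiority power is 84.9%. The metropolitan group is not short: 200 × 0.4 × 0.8 = 64, against 54.

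**The case against.** The strongest reply is that 162 may already be the number after losses. The sample-size section says that 162 will be included and ties the 20% to feasibility, and 200 × 0.8 = 160 fits that reading well. This has force: it means one cannot say that attrition was ignored. It does not settle the matter, because the abstract says that 162 will be recruited, and on the net reading the article's own 60% share leaves about 48 per randomised arm.

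A second reply is that the 20% is not a dropout rate. That is correct. It combines refusal with attrition. Under Participants and Randomization, families consent before they are allocated, so refusals cost no power. A reader might infer that the trial has been planned with 20% dropout and so has 80% and 73% power, or that neither stated figure can be delivered. The article does not support either inference, because it gives no rate of loss after randomisation.

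A third reply is that a condensed article may leave the split of the 20% to the full protocol, and that the planned longitudinal analysis could recover information from families without a week-12 score. Both points are fair. The missing split alone would not be a finding. But the article itself prints a required number, an equal recruitment number, an expectation of attrition and two power values, and these do not fit together. The power statements rest on two-group comparisons with 54 per group, and Statistical analysis describes the longitudinal work as a further, more detailed step. Analysis by intention to treat does not by itself supply missing week-12 scores.

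**Conclusion.** The point holds conditionally. The calculations are not wrong: 54 per arm and 87.2% both reproduce. What is unsettled is what 162 counts, and each reading leaves something to correct.

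- **162 recruited:** the stated power holds only with essentially no loss. Three families lost per arm already cost about 2 points for superiority (89.6% to 87.5%) and 3 for equivalence (87.2% to 84.1%). The worst case is 79.8% and 72.7%.
- **162 net of refusal and attrition:** the power figures stand on their own terms, but the abstract's recruitment statement is wrong. The caseload figures support about 48 per randomised arm, with about 85% power for superiority.

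These sizes assume SD 10, a difference or bound of 7.5, equal arms, and the two alpha conventions given in the working. The caseload check also assumes that all new diagnoses are eligible and that the 20% applies equally in both regions. The mismatch itself is certain; its size is bounded by the text but not fixed.

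**What to change.** State whether 162 is the number recruited or the number with week-12 data, and make the abstract and both parts of the sample-size section agree.

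- If it is the number recruited, say how much of the 20% is loss after randomisation and restate both power figures at the number then expected at week 12. For example, 49 per arm gives about 86% and 82%.
- If it is the number analysed, correct the recruitment statement in the abstract and check the 108 regional and remote families against the caseload figures in Background.

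When restating the equivalence power, say that it uses 1% per one-sided test, since 87.2% reproduces only on that convention.

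The cost is wording and a less favourable stated power. Restating the power needs no extra enrolment and no change of design.
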